## Abstract

**Background:**

Extensive studies have shown that older people are negatively impacted by impaired eating and nutrition. The abilities to eat, enjoy food, and participate in social activities associated with meals are important aspects of health-related quality of life (HRQoL) and recovery after illness. This project aims to (*i*) describe and analyze relationships between oral health and oral HRQoL, swallowing ability, eating ability, and nutritional risk among older individuals admitted to short-term care; (*ii*) compare the perceptions that older individuals and staff report on care quality related to oral hygiene and eating; and (*iii*) study the feasibility and effects of a training program for people with impaired swallowing (i.e., dysphagia).

**Methods/Design:**

This project consists of two parts, which will be performed in five Swedish counties. It will include approximately 400 older individuals and 200 healthcare professionals. Part 1 is a cross-sectional, descriptive study of older people admitted to short-term care. Subjects will be assessed by trained professionals regarding oral health status, oral HRQoL, eating and nutritional risk, and swallowing ability. Swallowing ability will be measured with a teaspoon test and a swallowing capacity test (SCT). Furthermore, subjects and staff will complete a questionnaire regarding their perceptions of care quality.

Part 2 is a cluster randomized intervention trial with controls. Older participants with dysphagia (i.e., SCT <10 ml/s, measured in part 1) will be recruited consecutively to either the intervention or control group, depending on where they were admitted for short-term care. At baseline, all subjects will be assessed for oral health status, oral HRQoL, eating and nutritional risk, swallowing ability, and swallowing-related QoL. Then, the intervention group will receive 5 weeks of training with an oral screen for neuromuscular training focused on orofacial and pharyngeal muscles. After completing the intervention, and at six months post-intervention, all assessments will be repeated in both study groups.

**Discussion:**

The results will make important contributions to rehabilitation knowledge, including approaches for improving swallowing function, oral health, and food intake and for improving the quality of oral care for older people.

**Trial registration:**

This trial was retrospectively registered at ClinicalTrials.gov, on July 4, 2016, identifier: NCT02825927.

## Background

During the last 20–30 years, researchers from various disciplines have provided extensive knowledge about the negative consequences associated with impaired oral health, nutrition, and eating ability in older people. For example, these impairments can lead to slower wound healing and increase the risks of developing pneumonia and other infections, pressure ulcers, and fall injuries [1–3]. Furthermore, being able to eat, to enjoy food, and to participate in the social activities associated with meals are important aspects of the quality of life (QoL) for older people [4, 5]. One important aspect of eating is the ability to swallow safely. The prevalence of impaired swallowing (i.e., dysphagia) is high among older individuals; thus, this impairment has been described as a “geriatric giant” [6]. The prevalence of dysphagia in older populations has been reported to be 11–80% [6], with variations among studies that depended on the degree of frailty in the cohort, the presence of neurological disease, and the evaluation method used. Many older people adapt slowly to dysphagia by eating slower and changing food consistency; thus, many hold the opinion that developing dysphagia is a natural consequence of aging [7]. In recent years, more attention has been directed toward swallowing rehabilitation, and different treatment designs have been developed to improve swallowing function [8, 9]. One promising method of swallowing rehabilitation is training with an oral screen, which has been shown to improve dysphagia significantly [10]. Another important aspect of eating is oral health. Good chewing function requires a sufficient number of healthy teeth or functioning prostheses for adequate occlusion. Without adequate chewing, it is difficult to comminute and digest the food, which results in impaired swallowing [11]. Daily oral care is essential for good oral health. Older people that cannot perform oral care alone become dependent on health care professionals, which have differential knowledge about oral health, ambitions, and priorities [12].

When older people that are chronically ill undergo treatment for an acute illness or hospital treatment, they often recover for weeks or months in intermediate- or short-term care facilities that provide basic nursing care [13]. In Sweden, this type of care can be provided in a short-term care unit, a residential setting, or a hospital (for intermediate care). Short-term care can also include support for older people, when they are in frail conditions and are waiting for care-home placement, undergoing rehabilitation, require recurrent relief for family members that are informal caregivers, and even when they require end-of-life care [14, 15]. Although thousands of older people are admitted yearly to Swedish short-term care units, there is little knowledge about the content of care and the effects on individual health, functioning, and quality of life [14, 15]. We also lack knowledge on how caretakers perceive the quality of care that they deliver. The scarcity of empirical studies on short-term care might be related to the expected methodological and ethical problems. For example, problems may be caused by the short care interval (individuals are admitted for only a few weeks), the frail state of older individuals, and the complex care organization. It has been suggested that conducting research in a short-term care context poses challenges related to obtaining informed consent, achieving sufficient power in intervention studies, and controlling for confounding factors, such as the different skill mixes and staffing levels in various care units [16]. In summary, there is an urgent need for new knowledge concerning the content, quality, and effects of short-term care for older people.

## Methods

### Aims and research questions

The overall aims of this multidisciplinary, multicenter project are (*i*) to describe and analyze relationships between oral health and oral health-related quality of life (HRQoL), swallowing ability, eating ability, and nutritional risk for older individuals admitted to short-term care; (*ii*) to compare the perceptions reported by older individuals and staff on care quality related to oral hygiene and eating; and (*iii*) to study the feasibility and effects of a training program for older people that exhibit dysphagia, but have different diagnoses.

The research questions we will address are:What is the state of oral health among the older people admitted to short-term care?What is the state of swallowing ability among the older people admitted to short-term care?How do the older people admitted to short-term care describe their oral health and their oral HRQoL?How do the older people admitted to short-term care describe the quality of their oral care?How do staff members in the corresponding short-term care unit describe the quality of oral care delivered?Which factors impact the perceptions of care quality held by older individuals and the staff?What are the differences and similarities between older individuals and the staff in their perceptions of care quality?How does systematic training with an oral screen device for 5 weeks affect impaired swallowing function?How do older people admitted to short-term care describe their swallowing-related QoL?Is there any correlation between oral health, eating ability, and swallowing ability in older people admitted to short-term care?

This project will provide data for three doctoral theses; one student is a registered nurse, RN (MA); one is a registered dental hygienist, RDH (SK); and one is a speech-language pathologist, SLP (PH). Detailed descriptions of the specific aims and research questions for each doctoral project will be presented with the results in separate articles.

### Design and setting

The SOFIA project consists of two main parts; part 1 is a descriptive, cross-sectional study (aims *i* and *ii*), and part 2 is a cluster randomized, controlled trial (aim *iii*).

Data collection will take place in 32 short-term care units, located in five Swedish counties, in both rural and urban areas. The short-term care units are diverse in organization and staffing; they may be one section of a care home or an independent short-term care unit.

Participating short-term care units will be selected, based on informed consent from the heads of social welfare services and unit managers; the number of beds; the estimated number of discharges per month; and the geographic location. The sample in part 1 will comprise approximately 400 older participants. All participants will be assessed at baseline, and participants that exhibit low swallowing capacity (i.e., <10 ml/s) will be asked to participate in the interventional part of the study (part 2). In part 2, participating older persons will, after informed consent, be randomized into either the intervention or the control group, based on where they were admitted for short-term care. In addition to the baseline assessments, all participants in part 2 will be assessed after the intervention is completed (5 weeks) and 6-months post-intervention. The follow-up assessments will be conducted at the study participant’s location (e.g., in the short-term care unit, in the individual’s own home, or in a care home, where the older person resides at that time).

### Ethics

This project has been planned in accordance with the Helsinki Declaration [17], was approved by the Uppsala Regional Ethics Review Board, Sweden (Dnr 2013/100), and was retrospectively registered with Clinical Trials.gov, on July 4, 2016 identifier: NCT02825927.

### Participants

#### Aged participants

All individuals admitted to the selected short-term care units will be eligible for study participation. Inclusion criteria include: residence in the short-term care unit for at least three days, age ≥65 years, able to understand and speak Swedish, and cognitive capacity (judged by nurses) sufficient to give informed consent and to participate in data collection. Individuals that receive end-of-life care will be excluded.

The inclusion criteria for participation in part 2 include: dysphagia, displayed at baseline with a teaspoon test; and a rate of <10 ml/s on the Swallowing Capacity Test (SCT) [18].

Eligible participants will be asked to provide informed consent, in accordance with the research ethics requirements outlined in the Helsinki Declaration [17].

#### Care unit staff

All staff members working in the corresponding short-term care units will be eligible for study participation, including licensed practical nurses, nurse aides, registered nurses, occupational therapists, and managers.

All staff members will be informed about the study and will be provided with questionnaires at staff meetings. All questionnaires will be anonymized and mailed back to one of the researchers after review. A completed questionnaire will be taken to indicate informed consent. The manager of the short-term care unit will be instructed to remind the staff members to complete the questionnaire after two and four weeks.

### Data collection

Data collection in project parts 1 and 2 will be based on clinical assessments and self-reported measures, conducted by formally trained professionals (seven RDHs, and two doctoral students; with the professions RDH and SLP). These professionals have received specific training on data collection and on instructing participants and staff about the intervention; i.e., the swallowing training. The data collection period is 2013–2017.

In project part 1, clinical assessments will record: (a) eating ability and nutritional risk, (b) oral health status, (c) swallowing ability, (d) functional status (i.e., activities of daily living), (e) biometric measures (e.g., body weight and height), medical diagnoses, and planned discharge destinations, based on social service and nursing documentation. Self-reported measures will include: (f) care quality related to oral health and eating, (g) oral HRQoL, and (h) swallowing-related QoL. In project part 2, clinical assessments will record: (a) eating ability and nutritional risk, (b) oral health status, (c) swallowing ability, (d) functional status, and (e) biometrics and where the participant is located at the time. The self-reported measures will include: (g) oral HRQoL and (h) swallowing-related QoL. Table 1 provides an overview of the validated instruments used for the data collection in project parts 1 and 2, and the time points when the assessments will be performed. For detailed information about the instruments, see the primary references shown in Table 1.

**Table 1 Tab1:** Instruments and measures to be implemented for data collection

Instrument	Reference	Outcome	Description	Time point
Katz Index of Activities of Daily Living (Katz-ADL)	[32, 33]	Functionality. Secondary outcome	Clinical assessment tool. Total score range: 1–7 (i.e., A-G), where 1 is “independent” and 7 is “very dependent”.	t1, t2, t3
Minimal Eating Observation and Nutrition Form –version II (MEONF-II)	[23, 24]	Risk of under-nutrition (UN), based on eating ability. Primary outcome	Clinical assessment tool. Total score range: 0 to 8, where 0–2 is no or low UN-risk; 3–4 is moderate UN-risk; ≥5 is high UN- risk.	t1, t2, t3
Quality of care from a patient’s perspective- modified version (QQP-modified version)	[19, 20]	Quality of care. Primary outcome	Self-reporting tool; 24 items. Each item is rated for both perceived reality (PR) and subjective importance (SI) with a 4-point Likert type scale. The PR range is: 1 (do not agree at all) to 4 (completely agree); the SI range is: 1 (little or no importance) to 4 (very highest importance). For each item, the PR and SI can also be rated ‘not applicable’ (58).	t1
Oral health status	Descriptive	Oral health.Primary outcome	Clinical assessment, which includes: an estimation of oral hygiene; a numeric registration of teeth; the presence of bridges, partial denture, full denture, implants; the number of occluding surfaces; and a record of the need for dental care. Also questions were asked about self-perceived oral health, whether there was an established dental contact, and the time since the most recent dental visit.	t1, t3
Revised Oral Assessment Guide (ROAG)	[25, 26]	Oral health status. Primary outcome	Clinical assessment tool, which includes 9 categories: voice, lips, mucous membranes, tongue, gums, teeth, dentures, saliva, and swallowing. Each category is described and graded on 3-point Likert scale: 1 indicates “healthy or normal condition”, 2 indicates “moderate alterations”, and 3 indicates “severe alterations”.	t1, t3
Oral Health Impact Profile (OHIP-14)	[28, 29]	Quality of life related to oral health. Secondary outcome	Self-reporting tool with 14 items in 7 categories. Each item is estimated on a 5-point Likert scale: 0 indicates “never” and 4 indicates “very often”.	t1, t3
The Swallowing Capacity Test (SCT)	[18]	Swallowing capacity. Primary outcome	A teaspoon test is carried out before the SCT. When signs of aspiration are observed, the SCT is not performed. Clinical assessment: the participant is instructed to drink 150 ml water from a glass as rapidly as possible, but safely, and to stop if any difficulty arises. Swallowing capacity is measured as the amount of water swallowed divided by the time it takes (ml/s). A capacity of ≥10 ml/s is considered normal. Signs of dysphagia will be recorded (e.g., coughing or wet/gurgling voice). When the subject fails the teaspoon test, a SCT score of 0 ml/s will be recorded.	t1, t2, t3
The Swallowing Quality of life Questionnaire (SWAL-QOL)	[30, 31]	Quality of life related to swallowing. Secondary outcome	Self-reporting tool with 44 items. Each item is rated on a 5-point Likert scale. Range: 1 “least favorable state” to 5 “most favorable state”. An additional 3 items are included for rating different types of food and drink consistencies and health status. These are rated on a 5-point Likert scale.	t1*, t2, t3

t1 = baseline; t1* = only older individuals with swallowing capacity <10 ml/s at baseline; t2 = immediately after the 5 week intervention; t3 = 6 months post-intervention

Data on external, objective care conditions, such as staffing, number of beds, length of stay, and prevalence of overcrowding, will be collected from the unit manager at each short-term care unit.

The nursing staff members’ perceptions of the quality of oral care and eating-related issues will be measured with a modified version of the Quality of care from a patient’s perspective questionnaire (QPP-Staff) [19, 20]. These data will be collected during a workplace meeting.

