### Sample size calculation

In study 2, the primary outcome variables will be the changes in swallowing capacity (based on the SCT), measured at the start and end of treatment, and at follow-up, 6 months later. The sample size calculation will be based on the assumption that the data will be normally distributed. To retain an overall type I error of 5%, the type I error will be set to 2.5% for the primary endpoint. Based on historical data, we assume that the standard deviation of the change in SCT level will be 3 ml/s. To detect a critical difference of 2.8 ml/s in swallowing capacity between the intervention and control groups with a power of 80% and type I error of 2.5%, a sample size of at least 22 subjects would be required to fulfill the study protocol in each group. The total number of subjects included must be somewhat higher, to compensate for drop-outs.

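### Table 1 does not say to which project part its primary labels apply, so it conflicts with the single primary measure in the sample-size section; whether 5% error control holds depends on which of the two governs

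*Protocol article*

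**What the plan says.** Table 1, under Data collection, is introduced as an overview for project parts 1 and 2 together and has one outcome column. Five instruments carry a primary label in it:

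- MEONF-II ("Risk of under-nutrition (UN), based on eating ability. Primary outcome"), at t1, t2 and t3;
- the descriptive oral health status record ("Oral health.Primary outcome"), at t1 and t3;
- ROAG ("Oral health status. Primary outcome"), at t1 and t3;
- SCT, at t1, t2 and t3;
- the modified QPP, at t1 only.

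The footnote defines t2 as directly after the five-week intervention and t3 as six months after it. Under Design and setting, part 1 is cross-sectional and only part 2 participants are followed up, so t2 and t3 belong to part 2 alone. Neither the table nor the text says which part a label refers to.

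Sample size calculation is specific to the trial: "In study 2, the primary outcome variables will be the changes in swallowing capacity (based on the SCT". Two post-baseline time points are named there, namely when treatment ends and half a year after that. On the error level the section states: "To retain an overall type I error of 5%, the type I error will be set to 2.5% for the primary endpoint".

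Statistical methods sets P below 0.05 as the criterion of significance and does not repeat the 2.5%. It applies Bonferroni to multiple pair-wise tests on one data set, without naming the outcomes that form a family.

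**The concern.** The protocol has to settle which outcomes are primary in the randomised trial, and here two sections can be read as giving different answers. The sample-size section gives one measure. Table 1 gives primary status to three further measures at follow-up visits that only the trial has, and none of the three has a stated error level or power calculation.

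At stake is what may be claimed as a primary result. With the labels as they stand, a part 2 difference in MEONF-II, ROAG or oral health status could be reported as a primary finding with Table 1 as support, although the error level was planned for SCT. The project feeds three theses whose specific aims are left to later articles, and registration was retrospective, so the article itself needs to be clear on this point.

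**Working it through.** **Step 1. Reproduce the plan's figure.** Inputs from Sample size calculation: difference 2.8 ml/s, standard deviation of change 3 ml/s ("we assume that the standard deviation of the change in SCT level will be 3 ml/s"), power 80%, type I error 2.5%. Sidedness is not stated, so two-sided is taken.

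n per group = 2 × (z₀.₉₈₇₅ + z₀.₈₀)² × SD² / difference² = 2 × (2.241 + 0.842)² × 9 / 7.84 = 21.8, so 22.

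This is the stated 22, with 80.3% power by the normal approximation. A one-sided 2.5% would give 19, so the plan's figure fits a two-sided 2.5%.

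**Step 2. What the 2.5% covers.** SCT change is compared at two time points.

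- Sum of levels: 2 × 0.025 = 0.05.
- Independent tests: 1 − 0.975² = 0.0494.

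So 2.5% retains 5% for exactly two tests. That the split is over the two time points is an inference; the section does not say so.

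**Step 3. Count the tests if the Table 1 labels apply to part 2.** Each instrument counts as one test per post-baseline visit.

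| Labelled primary | t2 | t3 | Tests |
|---|---|---|---|
| SCT | yes | yes | 2 |
| MEONF-II | yes | yes | 2 |
| Oral health status | no | yes | 1 |
| ROAG | no | yes | 1 |
| QPP | no | no | 0 |
| Total | | | 6 |

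**Step 4. Overall error for six tests.**

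- All at 2.5%, independent: 1 − 0.975⁶ = 0.141.
- SCT at 2.5%, the other four at 0.05, independent: 1 − 0.975² × 0.95⁴ = 1 − 0.9506 × 0.8145 = 0.226.

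The documents give no correlations. The values below are assumptions, simulated with equally correlated normal test statistics (1,000,000 draws).

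| Assumed correlation | All six at 2.5% | SCT at 2.5%, others at 5% |
|---|---|---|
| 0 (formula) | 14.1% | 22.6% |
| 0.3 | 13.0% | 20.6% |
| 0.5 | 11.2% | 17.8% |
| 0.8 | 7.5% | 12.2% |

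**Step 5. Consequence for size if six tests shared 5%.** Bonferroni gives 0.05 / 6 = 0.833% per test. SCT would then need 28 per group, and 22 per group would give 67.6% power (normal approximation).

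**Step 6. The level in Statistical methods.** If its 0.05 were applied to the two SCT tests in place of 2.5%, overall error for independent tests would be 1 − 0.95² = 9.75%.

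**The case against.** The strongest reply is that there is no loss of error control. The sample-size section is the only statement specific to the trial, and on its definition the 2.5% level does what it promises. Table 1 is an inventory of instruments for the whole project. QPP is labelled primary but collected only at baseline, so the label cannot always mean primary in the trial. The five labelled measures match the topics of aims (i) and (ii), which Design and setting assigns to part 1. The research question on the training asks only about swallowing function. The time-point column says when an instrument is used, not at which visit it is primary.

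Most of this stands. A reader might infer that the 2.5% split already fails to hold 5%. The documents do not support that: it follows only if the project-wide labels are taken as part 2 primaries, and no section lists six primary tests. Nor should an error rate of 26% (1 − 0.95⁶) be quoted, because it puts SCT at 0.05 against the sample-size section. Independence is also an upper-end assumption, since the same instrument at t2 and t3 will be correlated and ROAG contains a swallowing category. The Bonferroni rule in Statistical methods might cover some of these tests.

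What the reply does not do is remove the conflict. Nothing ties the extra labels to part 1. The outcome column also ranks SWAL-QOL, which is collected only from people below the part 2 threshold and then at t2 and t3. That suggests, without proving it, that the column ranks part 2 outcomes too. The Bonferroni rule is attached to no list of primary outcomes.

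**Conclusion.** The conflict over the trial's primary outcomes is real and should be resolved. Its effect on error control is conditional. Under the sample-size section, overall error stays at or just under 5%. Under the wider reading of Table 1 it would be about 14% to 23% for independent tests, and still about 7.5% to 12% at an assumed correlation of 0.8. These figures rest on six tests, one per instrument and visit; oral health status has several components, so testing them separately would raise the count. The sample size needs no change as long as SCT change remains the only part 2 primary measure.

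**What to change.** - In Table 1, mark which project part each outcome label applies to.
- For part 2, list SCT change (at t2 and t3) as the only primary measure, tested at 2.5% at each time point, and say that the 2.5% is split over these two.
- Label MEONF-II, ROAG and oral health status secondary for part 2. Keep their primary labels for the descriptive aims of part 1.
- In Statistical methods, carry over the 2.5% for the part 2 primary comparisons, since that section now states only P below 0.05.

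The cost is a table edit and a sentence or two. The 22 per group is unaffected. The downside is that part 2 results on MEONF-II, ROAG and oral health status can be claimed only as secondary.
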